### Laboratory analyses

2.5

The preoperative values of laboratory tests (BUN, CREA for renal function; AST, ALT for liver function, CRP, CK, CK MB, BNP for Cardiac function; HB, WBC, PLT, PaO2/FiO2, and PaCO2 for blood routine) in the last 7 days before operation were analyzed as baseline values (preoperative). Extra blood samples will be collected on day 1 after surgery for laboratory evaluation. Postoperative complications were evaluated by a doctor certified by an independent committee. In this trial, he will be guided on the diagnostic criteria for specific postoperative complications. The specialist will evaluate all participants until 30 days after surgery.

### Postoperative complications

2.6

A medical specialist, the outcome assessor, will be instructed about diagnostic criteria in this study for specific postoperative complications. All participants will be evaluated by the outcome assessor until 30 days after surgery. And we will use evidence-based process of comprehensive geriatric assessment (CGA)^[11]^ to evaluate an older patient's general condition and the risk of adverse outcomes

### Study outcomes

2.7

The degree of pain relief, the length of the first exhaustion, the time of the first meal, the length of hospitalization, and the incidence of complications would report.

### Adverse events

2.8

The most common adverse events in patients who died following a cancer resection were related to the surgical care, medical care, critical care, and staffing, communication and documentation.^[12]^ We will train the research personnel, implement the research plan strictly according to relevant regulations, and guarantee the quality of data collection.

### Withdrawal and dropout

2.9

The trial will be concluded at any stage when the main investigator considers that there is an unacceptable risk of serious adverse events, or the patient refused to continue, withdrew the consent, and violated the inclusion or exclusion criteria or trial protocol. Interim analysis will not be conducted; the patient's physical condition will be paid attention after recruitment. However, the hospital will develop the final criteria for early termination of the study, which may be based on clear evidence that one of the trial groups deteriorated, that there was no significant benefit of reasonable doubt in the measurement of the main outcome, as well as the existing literature and clinical understanding of the disease.

### Confidentiality

2.10

On recruitment, the researchers gave each participant an unique number, and only the number is used to identify participants. The information sheets and electronic documents collected will be used for security offices locked in any safe. The recipient list and notification approval form will be securely identified. All digital files will be password protected and stored securely. The trial sponsor has access to the final trial dataset.

### Statistical analysis

2.11

In this study, the sample size was estimated by comparing 2 independent samples. Considering the loss of follow-up, the sample size was increased by 10%, so the final sample size (N1 + N2) ∗ (1 + 10%) was 110. Therefore, 55 patients in the case group and 55 patients in the control were selected in this study. SPSS 22.0 statistical software was used for data entry and statistical analysis (*P* < .05 was statistically significant). Statistical description was used for general data, ANOVA of repeated measurement was used for quantitative data, and rank sum test was used for rank data.

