### Trial design

2.1

This will be a non-random control trail with single center experience. Elderly patients will be included from the Affiliated Hospital of Southwest Medical University. We developed this protocol based on the 2013 statement of standardized protocol interventions: recommendations for intervention trials (SPIRIT).^[10]^Figure 1 shows the schedule for registration, assessment, intervention, and follow-up in accordance with spirit guidelines.

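### For laboratory values taken only before surgery and on day 1, the prescribed repeated-measures ANOVA makes the preoperative value part of the outcome; in a non-random comparison its group main effect should not be read as an ERAS effect.

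*Protocol article*

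**What the plan says.** Section 2.11 of the protocol article assigns one method to all quantitative variables: "ANOVA of repeated measurement was used for quantitative data". It gives a general significance threshold of P below .05. It lists no time levels, no treatment contrast and no covariate.

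Section 2.5 (Laboratory analyses) describes two occasions for a set of blood tests that includes CRP. Preoperative values "in the last 7 days before operation were analyzed as baseline values (preoperative"), and "Extra blood samples will be collected on day 1 after surgery for laboratory evaluation". The text mentions no later laboratory sample.

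Section 2.1 fixes the allocation: "This will be a non-random control trail with single center experience". The Abstract also calls the trial non-random, although its Methods sentence says in the same breath that patients will be randomised. That inconsistency is a separate matter; the design section is followed here.

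On size, section 2.11 states that "the final sample size (N1 + N2) ∗ (1 + 10%) was 110", with "55 patients in the case group and 55 patients in the control were selected in this study".

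**The concern.** A two-group, two-occasion repeated-measures ANOVA produces three F-tests: group, time, and group-by-time. The group test compares each patient's average of the preoperative and day-1 values. A preoperative value cannot have been changed by surgery or by what follows it. Averaging it in has two consequences:

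- A difference that already existed before the operation is counted as part of the treatment effect.
- An effect that exists only on day 1 is cut in half.

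In a randomised trial the first consequence would be chance alone, so the group test would keep its error rate and only lose power. Here allocation is not random, so case mix can produce a real preoperative difference and, through it, a significant group term with no ERAS effect. The preoperative value is already being collected and could instead serve as a baseline.

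**Working it through.** **The plan's own figure.** 110 / 1.10 = 100, so N1 + N2 = 100, or 50 per arm before the 10% addition, and 100 × 1.10 = 110 agrees. The base of 100 cannot be reproduced, because section 2.11 says only that "the sample size was estimated by comparing 2 independent samples" and gives no effect size, SD or power. The checks below use 50 per arm (after the allowed loss) and 55 per arm (full recruitment).

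**Is the preoperative value an outcome level?** Repeated-measures ANOVA needs at least two occasions. Section 2.5 gives exactly two. If the preoperative value is taken out, one value per patient remains and nothing is repeated. On the visible text, applying the stated method to these values therefore makes the preoperative value an outcome level.

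**Inputs.** From the document: arm sizes, the 0.05 threshold (taken as two-sided), two occasions. Assumed, because the document gives none: SD 1 at both occasions, pre/post correlation ρ of 0.3, 0.5 or 0.7, and the imbalance and effect sizes shown.

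**Formulas.** Let d0 and d1 be the between-group differences before surgery and on day 1, with n per arm.

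- Group main effect: estimates (d0 + d1)/2; SE = √((1 + ρ)/n).
- Group-by-time (change): estimates d1 − d0; SE = √(4(1 − ρ)/n).
- ANCOVA of day 1 on group and preoperative value: estimates d1 − ρ·d0; SE ≈ √(2(1 − ρ²)/n).

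**Worked case, n = 50, ρ = 0.5.** The SEs are √(1.5/50) = 0.173, √(2/50) = 0.200 and √(1.5/50) = 0.173.

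- No ERAS effect, imbalance persisting at 0.3 SD (d0 = d1 = 0.3): the group term estimates 0.3, and 0.3/0.173 = 1.73, significant in about 40% of trials. Change estimates 0 and stays at 5%. ANCOVA estimates 0.3 − 0.15 = 0.15, significant in about 14%.
- True day-1 effect only (d0 = 0, d1 = 0.5): the group term estimates 0.25, and 0.25/0.173 = 1.44, power about 30%. Change gives 0.5/0.200 = 2.50, about 70%. ANCOVA gives 0.5/0.173 = 2.89, about 81%.
- No ERAS effect, a 0.5 SD imbalance that regresses to ρ × 0.5 by day 1 (d0 = 0.5, d1 = 0.25): change estimates −0.25, and 0.25/0.200 = 1.25, significant in about 24%. ANCOVA estimates 0 and stays near 5%.

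**Probability of P < .05 at 50 per arm** (20,000 simulated trials per setting; noncentral t for the group term in the first row). Each cell gives ρ = 0.3 / 0.5 / 0.7.

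| Situation | Group term | Group-by-time | ANCOVA |
|---|---|---|---|
| No effect, 0.3 SD imbalance persists | 45.3 / 40.3 / 36.4% | 5.0 / 5.1 / 4.9% | 18.5 / 13.9 / 9.4% |
| No effect, 0.5 SD imbalance regresses | 51.2 / 57.0 / 62.7% | 30.9 / 23.7 / 15.8% | 5.0 / 5.5 / 4.9% |
| True 0.5 SD effect on day 1 only | 33.5 / 30.4 / 26.6% | 55.7 / 70.2 / 89.0% | 73.6 / 81.5 / 93.2% |

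With no difference at either occasion, each test is significant in about 5%.

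**At 55 per arm**, the persisting 0.3 SD imbalance makes the group term significant in 44% (40-49% over the range of ρ). Power for the day-1 effect is 32% (29-36%) on the group term, 74% (59-92%) on change and 85% (77-95%) on ANCOVA. Together the two arm sizes give the ranges 36-49%, 27-36%, 56-92% and 74-95%.

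**At 30 per arm** (the Abstract's total of 60), the persisting 0.3 SD imbalance gives 24-29% on the group term. The conflict between 60 and 110 is a separate issue and does not change the conclusion.

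**The case against.** The strongest reply is that this is an omission in a condensed article rather than an error. Repeated-measures ANOVA contains the group-by-time term, section 2.11 never says that the group main effect will decide, and naming the deciding term is ordinary analysis-plan content. That stands: the missing label is not a finding. What remains is that the article does fix a method for these values, and that method gives the preoperative measurement no baseline role in a non-random comparison.

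A second reply is that section 2.5 itself labels the preoperative values as baseline. It does, but the method in section 2.11 has no place for a baseline, and without the preoperative value these tests have nothing repeated. The schedule figure is not shown, so further visits cannot be ruled out. For that reason the point is not extended to glucose, immune indices or the anxiety scale, whose occasions the text does not give.

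Third, the outcomes in section 2.7 are mostly out of reach. First exhaust, first meal, length of stay and complications have no preoperative value, so this mechanism cannot bias them. That stands and limits the importance of the point.

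Fourth, a reader might infer that any significant F-test may be claimed as benefit, which would give a false-claim rate of 1 − 0.95² = 9.75% per marker on the group and group-by-time terms together. The document states only a general threshold and no such rule, so that figure is not part of the point.

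Finally, group-by-time might be taken as the only valid contrast. The second row of the table shows otherwise: when the imbalance regresses, change is misleading and ANCOVA is not. When it persists, the reverse holds.

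**Conclusion.** The point holds for the laboratory values with a preoperative and a day-1 measurement. If the group main effect is read as the treatment effect, a persisting 0.3 SD imbalance with no ERAS effect yields significance in about 36-49% of trials. A true 0.5 SD day-1 effect has about 27-36% power, against 56-92% on group-by-time and 74-95% on ANCOVA. These figures assume 50-55 per arm, equal SDs, ρ between 0.3 and 0.7, and the stated imbalance and effect; none of the last three comes from the document.

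A reader might go further and conclude that the trial will report baseline imbalance as an ERAS effect. The document does not support that, because it does not say which term will be interpreted. This is a worthwhile and nearly free improvement to secondary laboratory comparisons, not a flaw in the main clinical outcomes.

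**What to change.** Add to section 2.11, for measures with both a preoperative and a postoperative value:

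> The between-group difference will be reported with a 95% CI in two ways: as the difference in change from the preoperative value to day 1 (the group-by-time term), and by ANCOVA of the day-1 value adjusted for the preoperative value. The group main effect is descriptive and is not evidence of an ERAS effect.

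State the limits alongside:

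- The change analysis is unbiased only if the baseline difference would have persisted unchanged. Otherwise, at 50 per arm, false positives run at about 16-31% for a 0.5 SD difference that regresses.
- ANCOVA is unbiased only if the difference regresses. Otherwise, at 50 per arm, they run at about 9-19% for a 0.3 SD difference that persists.
- Neither removes confounding by other factors, so where the two lead to different conclusions the result is to be reported as uncertain.

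The cost is a few sentences and one extra analysis per marker, with no new data or patients. The downside is that a significant group main effect can no longer be reported as benefit.

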### Trial oversight

2.12

The trial management team, including the lead investigator, test coordinator, test manager, data manager, and test statistician, maintains weekly contact. A meeting will be set by the Committee (TSC) at least once a month to check the progress of the trial and ensure that it is conducted in accordance with the protocol, relevant regulations and good clinical practice principles. In addition, a professional team will be set up to review the test schedule and safety data. The team will be independent of the experimental researchers and consists of 3 independent members, including 2 clinical experts and 1 trial statistician.

### Dissemination policy

2.13

Patient public participation members will play a key role in our findings. The results will be disseminated to patients, health professionals, committee members, policy makers, and the public widely. And the study will be published in Medicine. Conclusion strengthening postoperative recovery is an improved process of evidence-based nursing for surgical patients.

## Discussion

3

ERAS is a process of improving the condition of surgical patients based on evidence-based nursing. The implementation of strengthening postoperative recovery can greatly improve the clinical effect and reduce the cost, making eras an important standard of surgical value-based nursing.^[13]^ An article summarizes the ERAS results of elderly patients (≥65 years) after colorectal surgery. The median overall incidence rate is 23.5%, the median postoperative loss is 6 days, and the overall postoperative complication rate quite high. Conducting this review shows that it is challenging to compare postoperative complications between studies, and the exclusion criteria are different, because there is no uniform way to define or evaluate complications. Many studies only evaluate selected complications or range of complications by organ system. Patients receiving ERAS require lower upfront costs than traditional caregivers. However, the evaluation results of this study should be based on the long-term results and functional results of patient treatment, so the overall cost-effectiveness has not been fully determined, and longer follow-up data is required for further research. This review compare ERAS with routine care, in which primary outcomes including the degree of pain relief, the length of the first exhaustion, the time of the first meal, Length of stay, and the incidence of complications would report. In this study, we want to evaluate the clinical effect of ERAS and traditional care in elderly patients with colorectal cancer surgery through retrospective analysis of the results and risk factors for postoperative complications.

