The surgical team has developed and implemented multidisciplinary care programs, included ERAS, which improves patient outcomes and reduces hospital stay.^[6,7]^ ERAS includes evidence-based changes in traditional care, such as consultation before admission, avoiding mechanical bowel preparation, shortening fasting, carbohydrate drinks for 2 hours before surgery, avoiding fluid overload, minimally invasive surgery, avoiding early removal of drainage tubes, and catheters, and multimodality of opioid retention analgesia, early feeding and activities. In 1 meta-analysis, ERAS during colorectal surgery was significantly associated with the reduction of postoperative complications, total hospital costs, and early recovery of gastrointestinal function, without increasing 30 day readmission or mortality.^[8]^ Another study showed satisfactory short-term clinical results and demonstrated that laparoscopic D2 lymphadenectomy combined with era is safe and feasible.^[7]^ ERAS is widely accepted to be the gold standard for the treatment of colorectal disease in patients.^[8,9]^ However, there are few articles on the elderly. Our study intends to analyze the effectiveness and safety of clinical application of ERAS in elderly patients with colorectal cancer, and to observe its impact on postoperative recovery of elderly patients with colorectal cancer.

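### Five outcomes are called primary under one blanket P < .05 threshold, while early termination relies on a single main outcome that is never identified

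*Protocol article*

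**What the plan says.** Four places in the protocol article bear on which outcome decides the trial.

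- **Discussion.** It speaks of "primary outcomes including the degree of pain relief, the length of the first exhaustion, the time of the first meal, Length of stay". Complication incidence completes the list. That makes five outcomes under the label primary, and the word including leaves the list open.
- **Section 2.7, Study outcomes.** It gives the same five in the same order, ending with "the length of hospitalization, and the incidence of complications would report". None is ranked above another, and the word primary is not used.
- **Section 2.11, Statistical analysis.** It gives one threshold: "P* < .05 was statistically significant". Tests are assigned by type of data, not by outcome. The sample size comes from a comparison of two independent samples, with no outcome named.
- **Section 2.9, Withdrawal and dropout.** Early termination may rest on "no significant benefit of reasonable doubt in the measurement of the main outcome". This is one outcome, in the singular, and it is not identified here or elsewhere.

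Two further places matter for time of first meal. The Introduction describes ERAS in general as including "early feeding and activities". Section 2.3, which sets out what each group receives in this trial, covers guidance, bowel preparation, intraoperative warming and telephone follow-up, and does not mention feeding in either group.

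**The concern.** The document is inconsistent about how many outcomes decide the trial: five in the Discussion, one in section 2.9, and an unranked list in section 2.7. With a single flat threshold and no order among the five, a significant result on any of them could be reported as a positive primary result. The error rate for such a claim is then well above the nominal 5%. The stopping consideration in section 2.9 cannot be applied as written, because nobody can tell which outcome it refers to. For the same reason, no reader can say which claim the 110 patients are meant to support.

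There is a second, conditional worry. If early feeding is part of what the ERAS group receives, time of first meal partly records whether the programme was delivered. A difference there would not by itself show that patients did better.

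**Working it through.** **Inputs**

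- Number of outcomes called primary: 5 (Discussion; same list in section 2.7).
- Threshold for each: 0.05 (section 2.11). Sidedness is not stated; two-sided is assumed.
- Correlation between the five test statistics: not in the document. A common value ρ from 0 to 0.9 is assumed.
- All five null hypotheses true, with tests that are valid apart from multiplicity.

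**The plan's own figure.** The article states no overall error rate, so there is none to reproduce. The only computed figure is the sample size: 110 / 1.10 = 100 before inflation, and 100 × 1.10 = 110, or 55 per group. That step is consistent. The base of 100 cannot be reproduced, because no outcome, effect size, standard deviation, event rate or power is given.

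**Independent outcomes.** The chance of at least one P < .05 is 1 − (1 − 0.05)^5 = 1 − 0.95^5 = 0.226.

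**Correlated outcomes.** For normal test statistics with common correlation ρ and c = 1.96,

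chance = 1 − ∫ φ(u) · [Φ((c − √ρ·u)/√(1 − ρ)) − Φ((−c − √ρ·u)/√(1 − ρ))]^k du,

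where k is the number of true nulls. Numerical integration gives:

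| ρ (assumed) | k = 5 | k = 4 |
|---|---|---|
| 0 | 22.6% | 18.5% |
| 0.3 | 20.9% | 17.4% |
| 0.5 | 18.3% | 15.6% |
| 0.7 | 14.8% | 13.0% |
| 0.9 | 10.2% | 9.4% |

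The k = 4 column applies if time of first meal truly differs between groups, since only the other four can then yield a false positive.

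**After a change.** One primary outcome at 0.05 gives 5%. Five outcomes at 0.05/5 = 0.01 each give 1 − 0.99^5 = 4.9% under independence and at most 5% under any correlation. Holm's step-down procedure (0.05/5, 0.05/4, 0.05/3, 0.05/2, 0.05 on the ordered P values) keeps the same 5% bound and rejects at least as often.

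**The case against.** Several points can be made for the sponsor.

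*The word primary appears only in the Discussion, in a sentence that calls itself a review and follows a summary of another article.* True, and it leaves some ambiguity. But the sentence compares ERAS with routine care and repeats section 2.7's five outcomes in the same order, so it most likely describes this trial. If it does not, the article names no primary outcome, and the main outcome in section 2.9 is still undefined.

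*A multiplicity rule may sit in an analysis plan that is not shown.* Fair, and the absence of such a rule is not the point here. The point is what this article fixes: five primary outcomes in one place and one unnamed main outcome in another. An unseen plan does not remove that conflict from the text.

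*Section 2.11 does not say that each of the five is tested separately for a success claim.* Correct. That is read from the blanket threshold, the only one given, so the error rates are conditional on that reading.

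*The outcomes are related, so the inflation is smaller than it looks.* This stands in part. First exhaust, first meal and length of stay are plausibly correlated, and nothing in the article excludes values as high as 0.9. The rate there is about 10%, still twice nominal.

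A reader might infer that time of first meal must differ between the groups because ERAS prescribes it. The documents do not support that: early feeding appears in a general description of ERAS, and the trial's own intervention list is silent on feeding. A reader might also want to price an adjustment in lost power. The article gives no power and no effect size, so no such figure follows from it.

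**Conclusion.** The point holds. The article labels five outcomes primary, applies one flat threshold, and elsewhere depends on a single main outcome that it never names. If each of the five is judged at two-sided .05 and all nulls are true, the chance of at least one false positive is 22.6% under independence and about 10% at a common correlation of 0.9. It stays above 5% at every correlation examined.

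The independent figure follows from the article's own count and threshold; the others rest on assumed correlations. None of them is the trial's actual probability of a false claim. They cover multiplicity only, and section 2.1 describes the allocation as non-random, so bias between the groups comes on top and is not quantified here.

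The concern about time of first meal is conditional: it applies only if early feeding is part of the ERAS arm, which the Introduction and section 2.3 leave unresolved.

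**What to change.** 1. Name one primary outcome in section 2.7; the choice is the sponsor's. Use the same outcome as the main outcome in section 2.9 and as the stated basis of the sample size in section 2.11, and bring the Discussion into line.
2. Make the other four outcomes secondary, either with Holm adjustment or labelled as supportive. Holm across the four protects the secondary family only. If confirmatory claims across all five are to share one 5% error rate, test the secondaries only after the primary is significant.
3. Alternatively, keep all five as primary and apply Holm across them. In that case section 2.9 must say how its main outcome is to be read, and section 2.11 must say which of the five the sample size rests on.
4. Reconcile the Introduction and section 2.3 on whether feeding is part of the ERAS arm. If it is, report time of first meal as a process measure that cannot support an efficacy claim by itself, and take it out of the adjusted set.

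The cost is a text change in sections 2.7, 2.9 and 2.11 and the Discussion, plus the reconciliation with section 2.3. It needs no new data. The downside is that outcomes moved to secondary can no longer carry a headline claim; under the alternative, each outcome faces a stricter threshold, starting at 0.05/5 = 0.01 for the smallest P value.
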